## Abstract

**Background:**

Evening technology use (ETU) has been associated with sleep disturbances, often attributed to blue light exposure and cognitive arousal. However, most of the existing evidence focuses on younger populations and relies primarily on subjective measures. As older adults increasingly engage with both passive and active technology use, it is important to investigate how ETU impacts objective sleep. Currently, there is also a limited understanding of how particular evening digital activities, especially active versus passive engagement, affect objective sleep in older adults.

**Objective:**

This study aims to investigate the impact of exposure to ETU on both objective and subjective sleep outcomes in older adults.

**Methods:**

This is a randomized crossover trial involving approximately 55 adults aged 60‐75 years from the ongoing Swedish National Study on Aging and Care – Blekinge. Each participant will undergo 3 one-week intervention periods: active ETU, passive ETU, and a nondigital activity (book reading), with one-week washout periods in between. The order of interventions will be randomized. Sleep will be assessed using a home-based electroencephalography device (MUSE headband) and daily self-reports. Primary outcomes are sleep onset latency and wake after sleep onset. Secondary outcomes include objective measures such as total sleep time, sleep efficiency, and time spent in REM, deep, and light sleep, subjective sleep quality, adherence, and perception of the intervention and comfort of using the objective measurement tool, that is, the electroencephalography headband. Linear mixed-effects models (with fixed effects for condition and period and a random participant intercept) were used to analyze crossover effects on sleep outcomes.

**Results:**

Participant recruitment and data collection began in the fall of 2025 and will continue through summer 2026 or until the target sample size is reached. Data collection is scheduled to be completed by spring 2027. Results will include participant flow, baseline characteristics, adherence data, and comparative analyses of the 3 intervention conditions. Within-subject statistical models will be used to evaluate differences in sleep outcomes and investigate the associations between ETU and sleep quality.

**Conclusions:**

This crossover study will clarify how active and passive ETU, compared with a nondigital activity, relate to objective sleep in older adults. Findings will inform simple, practical recommendations for technology use before bed in late life.

## Introduction

The digital society has made it easy for its citizens to use technology for multiple purposes, from everyday tasks such as banking to entertainment, relaxation, and promoting health. Recent data indicate that about 90% of Swedes aged 60 years and older use the internet, with approximately 75% using the internet daily, showcasing digital engagement in later life [1], raising important questions about how this use may influence restorative behaviors such as sleep. In particular, evening technology use (ETU) before bed often becomes a routine; therefore, it is important to clarify its effects on sleep in order to protect sleep health among older adults.

Sleep is an important determinant of health and well-being, particularly in older adults, who may experience changes in sleep architecture and quality due to aging and lifestyle factors [2]. Even factors such as technology use may shape these sleep patterns. The increasing use of technology within the general population and among older adults [1], especially ETU and its potential effects on sleep, has raised concerns among health care professionals and researchers. Traditionally, these concerns have focused on the impact of bright light or blue light on melatonin release, which can disrupt the circadian rhythm. However, this unidirectional view has been refined by a bidirectional model that recognizes that technology can disrupt sleep and vice versa through multiple mechanisms. These include sleep time displacement, the arousal hypothesis, and the bright light hypothesis. Consequently, poor sleep can also lead to increased technology use, as it fills the time and provides cognitive distraction [3]. According to the arousal hypothesis proposed by Bauducco et al [3], using engaging or active digital content close to bedtime (eg, video games or social media exchanges) increases a person’s physiological and psychological arousal by increasing heart rate, alertness, or stress levels before bed. This, in turn, makes it harder to fall asleep quickly or stay asleep.

Existing research also highlights the influence of digital device use on sleep through mechanisms such as blue light exposure [4], cognitive stimulation [5], and emotional arousal [6,7]. Much of the current research on technology and sleep focuses on children, adolescents, and younger adults [8-10]. Far fewer studies have investigated whether and how these mechanisms generalize to older adults.

Older adults use technology for social interaction [11], entertainment [12], cognitive exercises [13], and overall well-being [14]. Older adults between the ages of 60 and 75 years are often overlooked in current research on sleep. This age group is old enough to experience age-related changes in sleep patterns, yet young enough to minimize the effects of frailty, multiple health conditions, and the use of multiple medications, which could skew the results. Additionally, their experiences with technology and sleep may differ from those of younger populations [15].

Additionally, little is known about how the type of ETU, whether passive (such as watching a documentary) or active (such as playing a video game), affects sleep compared with traditional, nondigital presleep habits. There has been some research that suggests that watching nature videos can promote relaxation, reduce stress, and have positive effects on cognitive and emotional health [10], which are factors that could positively influence sleep quality. Furthermore, it has also been shown that engaging in complex cognitive tasks before sleep can significantly improve both objective and subjective sleep quality, particularly for individuals who typically struggle with sleep issues [11]. On the other hand, video gaming before bed is associated with delayed sleep onset in adolescents [7]. Conversely, some research suggests that casual gaming may not significantly disrupt sleep, indicating that the type and intensity of gaming matter [8,16]. Moreover, to measure sleep objectively is important as it provides reliable, instrument-based evidence of sleep health that complements subjective reports and reduces bias [17,18]. Therefore, the aim of the study is to investigate the impact of exposure to ETU on both objective and subjective sleep outcomes in older adults.

## Methods

### Objectives

### Study Design

This study adopts a crossover randomized controlled trial (RCT) to examine how ETU influences objective and subjective sleep in older adults aged 60 to 75 years. Three conditions will be compared: (1) passive ETU, (2) active ETU, and (3) nondigital activity.

After completing an initial baseline assessment via survey, participants will undertake a 5-week schedule composed of 3 separate, one-week intervention periods. At baseline, each participant is randomized to one of six possible sequences of the 3 conditions (passive ETU, active ETU, nondigital; 3!=6). Participants then complete 3 one-week intervention periods in their assigned order, separated by 2 one-week washouts (total duration: 5 wk). We chose a 7-day washout period because systematic reviews of digital detox interventions often recommend this duration for detoxification [19].

During each intervention week, participants will maintain a daily evening log to record subjective sleep quality, ETU, and the comfort of using a wearable headband. Objective sleep outcomes will be assessed using electroencephalography (EEG) collected via a headband (Muse-S Athena, InteraXon, Toronto, ON, Canada), while self-reported logs capture subjective experiences. This crossover design allows for within-subject comparisons, thereby reducing variability, controlling for individual differences in sleep patterns, and confounding factors, while enhancing statistical power.

### Population and Recruitment

Participants in this study will be recruited from the Swedish National Study on Aging and Care – Blekinge (SNAC-B) cohort. SNAC-B is part of a large, national, population-based research initiative in Sweden focused on individuals aged 60 years and older [20]. The study is conducted at the Research and Development Clinic affiliated with the Department of Health at Blekinge Institute of Technology (BTH).

The SNAC-B population offers a well-characterized cohort of older adults, increasing the likelihood of identifying individuals who meet the inclusion criteria for this study. Eligible participants will be directly contacted by the research team, ensuring both transparency and voluntary participation. Detailed study information will be provided before obtaining informed consent.

Participants eligible for inclusion in the study will be aged between 60 and 75 years and must be regular users of digital devices such as smartphones or tablets. They should be willing and able to use an EEG headband for sleep monitoring throughout the intervention period. Additionally, participants must be able to take part in either the RCT, follow-up interviews, or both, depending on study needs and personal preference.

Individuals will be excluded from participation if they have a diagnosed sleep disorder or severe cognitive impairment. Use of medications that significantly influence sleep, such as melatonin or benzodiazepines, will also serve as an exclusion criterion.

Eligible participants aged 60‐75 years will be identified from the SNAC-B cohort. A random number will be generated using Excel to generate a random order of potential participants, who will be contacted sequentially until the target sample size of 55 is reached. One investigator ([name]) generated the randomization list for the 6 possible condition sequences using computer-generated random numbers in Excel. Random numbers, not participant IDs, determined assignment. Sequence codes were kept in a secure file on the university’s server and accessed only by the authors of this study.

### Intervention

#### Overview

This study uses a crossover RCT design in which participants progress through 3 different intervention conditions: passive ETU, active, and nondigital activity, in a randomized order. Each intervention phase lasts for one week, followed by a one-week washout period to reduce carryover effects, resulting in a total study duration of 5 weeks (Figure 1).

**Figure 1. F1:**
[figure not shown]
Schematic of the randomized crossover trial design. Participants complete three 1-week conditions in randomized order, separated by 1-week washout periods, following baseline investigation.

#### Baseline Assessment

Before the first intervention phase, participants complete a baseline survey (in Swedish language) assessing sociodemographic characteristics, subjective sleep health, chronotype, lifestyle factors, sleeping habits, general health status, and technology use (Multimedia Appendix 2).

#### Main Intervention

Participants will engage with the assigned evening activity for 30‐60 minutes within the final 60 minutes before intended bedtime. To minimize variability in the interventions, the digital activities are standardized. To reduce the likelihood of accidentally falling asleep, participants should complete the evening activity seated (not lying in bed) and move to bed only when ready for lights-out. If they fall asleep during the activity before starting the MUSE recording, they should start the recording as soon as they notice and select “fell asleep before recording” in the morning survey. For all technology sessions, participants will set the device display to medium brightness (≈50% of the slider) at the start of the activity and maintain this setting throughout. Auto/adaptive brightness should be turned off to prevent fluctuations. The activity may continue until the participant is ready to sleep (lights-out). Immediately before lying down to sleep, participants will put on the MUSE headband, start the recording, then switch off the lights and attempt to sleep. No additional screen use is permitted after recording starts. Compliance will be checked through self-reporting in the daily log.

#### Passive Evening Technology Use

Participants watch a curated selection of soothing documentaries, those narrated by Sir David Attenborough or the secrets of the forest on SVT Play, for 30‐60 minutes each evening, one hour before bedtime, using smartphones or tablets.

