#### Active Evening Technology Use

Participants engage with the interactive word-based game Ruzzle for 30‐60 minutes each evening, one hour before bedtime [2], using smartphones or tablets. It is to provide mental stimulation and engage participants actively.

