#### Nondigital Activity

Participants read a nonfiction book of their choice for the same duration, avoiding all digital screens for one hour before bedtime.

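### Neither the device nor other screen use in the final hour is held constant between the two technology weeks, so the key secondary active-versus-passive contrast can be biased or diluted if either goes with condition

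*Protocol article*

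**What the plan says.** All places are in the Protocol article.

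- **Device.** Passive Evening Technology Use has documentaries watched "one hour before bedtime, using smartphones or tablets". Active Evening Technology Use has the word game played "using smartphones or tablets. It is to provide mental stimulation and engage participants actively". Neither section, nor Main Intervention, asks for the same device in both weeks.
- **Standardization and light.** Main Intervention states: "To minimize variability in the interventions, the digital activities are standardized". It adds that "participants will set the device display to medium brightness", about half of the slider, with automatic brightness switched off.
- **Activity window.** The activity takes 30-60 minutes and falls "within the final 60 minutes before intended bedtime".
- **Other screens.** The reading week requires "avoiding all digital screens for one hour before bedtime". For the technology weeks the only limit given is "No additional screen use is permitted after recording starts".
- **Use of the contrast.** Table 1 lists active versus passive as a key secondary question. The Statistical Analysis Plan section models condition and period as fixed effects with a random participant intercept. Neither device nor other screen use enters the model.
- **Adherence.** Table 1 counts nights with at least 30 minutes of the activity.

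**The concern.** A participant may watch documentaries on a tablet in one week and play the game on a phone in the other. The two weeks then differ in screen size and light as well as in activity. A slider position is relative to the device, so half brightness on a phone and on a tablet need not give the same light.

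A participant may also do 30 minutes of the assigned activity and spend the other 30 minutes on a different screen use, including the kind assigned in the other week. Such a night counts as adherent.

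Randomizing the order of conditions balances time and order. It does not balance something that happens inside a condition and goes with it, and the model has no term to adjust for it. The Discussion (Principal Findings) names screen light and engagement as two routes to arousal and wants to learn whether effects belong to the activity. At stake is whether an active-passive difference can be read as an effect of activity type, and whether a null result can be told apart from dilution.

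**Working it through.** The plan gives no figure on this point to reproduce. The details of its power analysis are in an appendix that is not shown. The numbers below show scale only.

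**Inputs from the document:** n = 55; final window 60 min; assigned activity 30-60 min.

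**Assumed inputs:** device effect on sleep onset latency (SOL) 3-5 min; residual SD of a participant's weekly value 8 min; net device imbalance 10-40%; 30% of participants mixing screen uses; effect proportional to exposure time.

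**1. Unassigned share of the final hour**

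(60 − 60)/60 = 0% to (60 − 30)/60 = 50%, that is up to 30 minutes.

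**2. Standard error of the pairwise contrast**

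SE = SD × √(2/n) = 8 × √(2/55) = 1.53 min. It scales with the assumed SD (about 0.19 × SD).

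**3. Bias from device choice**

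Bias = net imbalance × device effect. Net imbalance is the share switching in one direction minus the share switching in the other. Participants who keep one device contribute nothing, and opposite switches cancel.

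| Net imbalance | Device effect | Bias | Bias / SE |
|---|---|---|---|
| 0% | any | 0 | 0 |
| 10% | 3 min | 0.3 min | 0.20 |
| 20% | 5 min | 1.0 min | 0.66 |
| 40% | 3 min | 1.2 min | 0.79 |
| 40% | 5 min | 2.0 min | 1.31 |

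At 40% net imbalance with no true activity effect, the two-sided 5% test would reject about 12% to 26% of the time (normal approximation, no multiplicity adjustment). The planned Tukey adjustment would lower these rates.

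**4. Dilution from mixed use**

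Let a participant spend *a* minutes on the assigned type and *b* on the other type, in both weeks. The share of the contrast kept is (a − b)/60.

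- 30 + 30 min: (30 − 30)/60 = 0. With 30% mixing, 0.70 × 1 + 0.30 × 0 = 0.70 of the contrast remains, and 0.70² = 0.49 of the information.
- 45 + 15 min: (45 − 15)/60 = 0.50. With 30% mixing, 0.70 + 0.30 × 0.50 = 0.85 remains, and 0.85² = 0.72 of the information.

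The first case is the worst case for that 30%.

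**5. Precision of a same-device analysis**

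If 40% switched device, 55 × 0.60 = 33 remain, and SE = 8 × √(2/33) = 1.97, about 2.0 min.

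**The case against.** The protocol does standardize a good deal: one game, a curated set of documentaries, a seated position, a common slider setting without automatic adjustment, and the same two device types in both weeks. It presents the home setting as naturalistic, so letting people use their own device is defensible. The Discussion disclaims inference about mechanisms and expects more screen exposure in the active week, so some exposure difference is part of the condition. Nothing in the document shows that device choice follows activity. The daily log and participant instructions are not reproduced in the text; they may already record the device or advise on it.

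Much of this stands, and it rules out several stronger readings:

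- A reader might infer that the primary result is compromised. It is not: the primary contrast pools both technology weeks against reading, and extra screen use in those weeks is still evening technology use.
- A reader might take the share of participants who switch device as the driver of bias. Only the net one-directional imbalance matters.
- A reader might take 70% of the contrast, or 49% of the information, as the expected loss. It is the worst case for the assumed 30%.
- A reader might call the statement on standardization false. It is incomplete on device and on the rest of the hour, which is a lesser fault.

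Two parts of the objection do not answer the point. Attributing a difference to the activity, even without a mechanism, still requires that the device not vary with it. The expectation of higher screen exposure in the active week is not secured either: documentaries on a tablet and the game on a phone would work against it. A log entry would help to measure the problem but would not prevent it.

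**Conclusion.** The point holds for the key secondary active-versus-passive contrast, as a weakness that can arise under the plan as written and not as a demonstrated bias. Device may differ between the two weeks within a participant, and up to half of the final hour is free for other screens in those weeks only. The slider rule reduces the light difference without removing it.

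Under the stated assumptions the device bias runs from zero (no net imbalance) through 0.3-1.0 min at 10-20% to 1.2-2.0 min at 40%. Only the upper end of that range approaches or exceeds the standard error of about 1.5 min. With 30% of participants mixing uses, 70% to 85% of the contrast remains for the two patterns worked above. The device effect, SD, imbalance and mixing share are not given in the document, so these sizes are illustrations. The case for acting rests on the small cost of the change and on recruitment still being open.

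**What to change.** 1. State in Main Intervention that each participant uses one and the same device in both technology weeks, and record which device it was.
2. Reconcile Main Intervention with the three activity sections on other screen use in the final hour, and word the timing of the activity alike throughout. Which rule applies is for the investigators to decide.
3. Report device and other-screen minutes by condition, from the daily log where it already captures them. Study Design says that the log records evening technology use.
4. Add a sensitivity analysis of the active-passive contrast in participants who used the same device in both weeks. State its lower precision (SE about 2.0 min if about 33 remain) and that device data for those already treated may rest on recall.

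The cost is one line of instruction, possibly one log field, and slightly less freedom for participants. The outcomes and the main model stay as they are.

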#### Active Evening Technology Use

Participants engage with the interactive word-based game Ruzzle for 30‐60 minutes each evening, one hour before bedtime [2], using smartphones or tablets. It is to provide mental stimulation and engage participants actively.

#### Nondigital Activity

Participants read a nonfiction book of their choice for the same duration, avoiding all digital screens for one hour before bedtime.

#### Daily Logs

Throughout each intervention week, participants maintain a daily log (in Swedish) of their intervention adherence, morning assessments of subjective sleep quality, and the feasibility or comfort of using the EEG headband. The daily survey also includes an open-ended item asking whether anything unusual since the prior evening could have affected sleep, with examples written such as more caffeine than usual (especially after ≈4 PM) and alcohol (Multimedia Appendix 2).

### Measures

The baseline and daily log surveys, along with the sociodemographic and subjective measures, are attached in MultimediaAppendices 2  3.

#### Sociodemographic and General Measures

The included variables were age, gender, living status, economic situation, employment situation, education, health status, sleep health scores, and the reduced Morningness–Eveningness Questionnaire (for chronotype) [22,23] (MultimediaAppendices 2  3 contain detailed questions).

#### Primary Outcome Measures

##### Overview

The primary outcomes of this study focus on changes in objective sleep onset latency (SOL) and wake after sleep onset (WASO) assessed using objective data collected via the MUSE EEG headband. This wearable device records brainwave activity throughout the night, enabling detailed analysis of various sleep parameters. The primary sleep parameters are provided below.

##### Sleep Onset Latency (SOL)

This refers to the duration of time it takes for a participant to transition from full wakefulness to sleep. Sleep latency will be automatically calculated by the MUSE EEG headband as the time from the start of recording to the first detected epoch of NREM sleep.

